## Abstract

**Background:**

Suboptimal translation of valid and relevant information in clinical practice is a problem for all health systems. Lack of information independent from commercial influences, limited efforts to actively implement evidence-based information and its limited comprehensibility are important determinants of this gap and may influence an excessive variability in physicians' prescriptions. This is quite noticeable in Italy, where the philosophy and methods of Evidence-Based Medicine still enjoy limited diffusion among practitioners. Academic detailing and pharmacist outreach visits are interventions of proven efficacy to make independent and evidence-based information available to physicians; this approach and its feasibility have not yet been tested on a large scale and, moreover, they have never been formally tested in Italy.

**Methods/Design:**

Two RCTs are planned:

1) a two-arm cluster RCT, carried out in Emilia-Romagna and Friuli Venezia Giulia, will evaluate the effectiveness of small group meetings, randomising about 150 Primary Care Groups (corresponding to about 2000 GPs) to pharmacist outreach visits on two different topics. Physicians' prescriptions (expressed as DDD per 1000 inhabitants/day), knowledge and attitudes (evaluated through the answers to a specific questionnaire) will be compared for target drugs in the two groups (receiving/not receiving each topic).

2) A three-arm RCT, carried out in Sardinia, will evaluate both the effectiveness of one-to-one meetings (one pharmacist visiting one physician per time) and of a 'new' information format (compared to information already available) on changing physicians' prescription of specific drugs. About 900 single GPs will be randomised into three groups: physicians receiving a visit supported by "traditional" information material, those receiving a visit with "new" information material on the same topic and those not receiving any visit/material.

**Discussion:**

The two proposed RCTs aim to evaluate the organisational feasibility and barriers to the implementation of independent information programs led by NHS pharmacists. The objective to assess a 10 or 15% decreases in the prescription of the targeted drugs is quite ambitious in such 'natural' settings, which will be minimally altered by the interventions themselves; this in spite of the quite large sample sizes used comparing to other studies of these kind. Complex interventions like these are not easy to evaluate, given the many different variables into play. Anyway, the pragmatic nature of the two RCTs appears to be also one of their major strengths, helping to provide a deeper insight on what is possible to achieve – in terms of independent information – in a National Health System, with special reference to Italy.

**Trial registration:**

ISRCTN05866587 (cluster RCT) and ISRCTN28525676 (single GPs RCT)

## Background

Information that doctors receive on benefits and risks of currently used drug treatments generally comes, either directly or indirectly, from the pharmaceutical industry [1-3]. It may thus be unsystematic and biased [4], and may be a component of the (often observed) excessive variability in physicians' prescriptions [5,6], uneasy to explain if one merely looks at evidence-based findings in medical literature.

In recent years the Italian Ministry of Health has made efforts in expanding physicians' access to independent and evidence-based information, like freely distributing the Italian translation of Clinical Evidence and enhancing the quality of the already freely distributed NHS Drug Information Bulletin. Nonetheless, sub-optimal diffusion of independent scientific information is apparent, as well as its comprehensibility to physicians who do not generally have epidemiology and statistics in their medical school background [7-11]. Improving access to, as well as comprehensibility of, evidence-based information remain important goals for Health Authorities, both at national and local levels.

However, simple diffusion of information – even if "evidence-based" – does not seem to affect prescribing behaviour, whereas active interventions like educational outreach visits to doctors (either one to one or small groups meetings), often employing pharmacists, seem more effective especially when clinical information is supplemented by prescribing data, according to an "*audit & feedback*" method [12-16].

Hence, in Italy there is room for improving independent information initiatives, promoting an active outreach system and a different role for NHS pharmacists, the latter being too often confined in administrative/auditing roles. There is also room for improving comprehensibility of medical information, which is infrequently targeted to "average" doctors and hardly ever offered in a clear, direct and appealing fashion, looking at the context of clinical practice [17].

The available evidence on the effectiveness of outreach visits comes from the English speaking world (United Kingdom, Canada, Australia, United States), whereas no studies have formally evaluated their effectiveness, feasibility and perceived usefulness in Italy [12-14]. For this reason, two pragmatic randomised controlled trials (RCTs) are proposed to carry out this complex evaluation in different settings: the first one, carried out in Emilia-Romagna and Friuli Venezia Giulia, will be a cluster RCT evaluating whether information meetings led by pharmacists with small groups of physicians change their prescribing behaviour, attitude and knowledge (being a cluster design the most appropriate to address the issue of contamination between groups); whereas the second one, carried out in Sardinia, will be a RCT evaluating one to one visits and the added value of a new format in improving doctors' knowledge, attitudes and prescribing practice [17].

Two more reasons to carry out these studies are that they would represent an unprecedented effort to accomplish such evaluation on quite a large scale, considering that three Italian regions would participate (Emilia Romagna with about 1500 physicians, assisting a population of about 2 million inhabitants; Friuli Venezia Giulia with about 400 physicians, assisting a population of about 400,000; and Sardinia with about 900 physicians, assisting a population of about 1 million) and that these interventions would be carried out in a 'natural' organizational setting, which would be minimally altered by the interventions themselves.

### Objectives

Overall, the two studies will specifically evaluate:

• whether information meetings with small groups of physicians (in Emilia-Romagna and Friuli Venezia Giulia) or with single physicians (in Sardinia), led by pharmacists and organised by Local Health Authorities within a large scale independent information program involving all local GPs, is organisationally feasible (and how barriers can be reduced)

• whether such programs can be effective in changing physicians' prescribing behaviour

• whether the provided information can also modify knowledge and attitudes of physicians on benefits and risks of the drugs under scrutiny (in Emilia-Romagna and Friuli Venezia Giulia)

• whether the format of information can affect the outcomes, specifically: whether an "enriched" format targeted at the average GP can improve knowledge, attitudes and prescribing behaviour more than a "traditional" format (in Sardinia)

• whether an active role of a GP (delegate by the PCG) in information meetings is feasible and useful (in Emilia-Romagna and Friuli Venezia Giulia)

## Methods/Design

### Study population

#### Emilia-Romagna and Friuli Venezia Giulia study (cluster RCT)

Primary Care Groups (PCGs) will be the unit of randomisation (cluster). PCGs are defined as small groups, ranging from about 10 to 20 general practitioners (GPs) and assisting about 8,000 to 25,000 people in a defined area. A general rule is to include PCGs with less than or equal to 20 GPs. Exceptions may be accepted (considering the pragmatic nature of the study) but should be adequately justified by Local Health Authorities recruiting them. In any case, the proposal to split groups with more than 20 subjects will be made.

Local Health Authorities, which are in charge of the local organization of the study, should actively promote the information meetings by making them part of compulsory education and/or providing CME credits.

#### Sardinia study (randomising single GPs)

Single GPs will be the unit of randomisation. All GPs are eligible, provided that their Local Health Authority has an organised system for tracking their prescriptions made within the NHS till the 5^th ^ATC level, in order to evaluate these prescriptions and to provide doctors with feedback. As in the first study, Local Health Authorities should actively promote the outreach visits among single GPs.

### Intervention/Exposure

#### Emilia-Romagna and Friuli Venezia Giulia study (cluster RCT)

A cluster RCT will be performed. PCGs will participate to two rounds of small group information meetings where a trained pharmacist, possibly supported by a GP (a "referent", delegate by the PCG), will provide information, discussing the contents of a bulletin specifically developed about the main studies/literature available on benefits and risks of drugs for preventing and/or curing a specific disease (enriched format) [17].

Within each round of visits (taking place in spring and autumn of 2007, respectively), PCGs will be randomised in two groups: those receiving information about a specific topic and those not receiving it (Fig. 1). To improve acceptability to Local Health Authorities and sample efficiency, PCGs not receiving information about one specific topic (e.g. topic A) will receive another topic (e.g. topic B). Two evaluations will then be carried out: for topic A related outcomes, recipients vs non recipients of topic A will be compared; conversely, for topic B related outcomes, the comparison will be between recipients vs non recipients of topic B.

**Figure 1 F1:**
[figure not shown]
Design of the cluster study (Emilia-Romagna and Friuli Venezia Giulia): effectiveness of information meetings.

Considering two rounds of information meetings, four topics will be needed (two topics each round) and four interventions will be tested overall. While these are different specific comparisons, the same general hypothesis will be tested: whether information meetings led by pharmacists are effective in changing physicians' behaviour (comparing to no visit on the same topic). The reasons why four comparisons are planned are to better evaluate the feasibility of this kind of intervention (which could be eventually proposed in the Italian NHS on a routine basis) and to have better insight into its effectiveness, since this may depend on the kind of topics and on the extent of information presented.

The first couple of topics chosen (for the spring 2007 round) are: 'drugs for the treatment of benign prostatic hyperplasia', and 'drugs for the primary prevention of osteoporotic fractures in elderly people'. The second couple of topics will be chosen about two-three months before the autumn 2007 round and this choice will depend, as well as for the first two topics, on relevance for clinical practice, limited availability and diffusion of information independent from drug industry, possibility to synthesize clear and evidence-based messages on benefits and risks of therapies and possibility to affect drug prescriptions significantly.

Stratified randomisation will be carried out within each Local Health Authority (LHA), using the number of assisted population per PCG (under or over the mean for that LHA) as stratifying factor. Pharmacists will be randomised along with the PCGs since the meeting scheme (which pharmacist meeting which PCG) will be defined before randomisation: this in order to avoid a 'topic-based' self-selection of visiting pharmacists, which may introduce a bias (doctors receiving intervention A could meet more or less motivated pharmacists, than those receiving intervention B).

About one pharmacist every 8–10 PCGs will get ad hoc training for the study, getting:

• one four-day intensive course (36 hours) on EBM methodology

• one three-day course (about 20–22 hours) for each of the four selected topics, discussing about the benefits and risks of drugs used in the correspondent clinical area and their relevance to clinical practice, looking at the available studies and at their internal/external validity.

Each PCG will nominate a "referent" GP to support pharmacists during the information meetings. Referents will get a half-day training module each round on the topic their group has been randomised to.

#### Sardinia study (randomising single GPs)

A three-arm RCT is planned: single GPs will be randomised so that they may receive: an outreach visit from a trained pharmacist, supported by information material in a 'traditional' format as background material; the same kind of visit supported by an 'enriched' format (the type of bulletin used in the cluster study) [17]; or no visit at all (Fig. 2). Both the effectiveness of the outreach visit and of the information format will be evaluated (see outcomes).

**Figure 2 F2:**
[figure not shown]
Design of the single doctor study (Sardinia): effectiveness of outreach visits and of two different formats.

Two rounds of visits are planned in this study too, each focusing on one topic. Therefore, only two topics will be addressed overall (comparing to four used for the other study). The first topic chosen is 'drugs for the treatment of benign prostatic hyperplasia'.

The 'traditional' material for this round has been selected considering its availability and diffusion and its recognised dependability. Two articles on that topic available in other drug bulletins have been eventually translated into Italian to be used for this scope: they appeared on the issue n. 252 of La Revue Prescrire ^® ^and on the issue n. 58 of Therapeutics Letter ^® ^About one pharmacist every 80 GPs will receive the same training as the pharmacists in the other study.

A graphical display of study design is shown in fig. 1 (cluster RCT) and fig. 2.

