1. for benign prostatic hyperplasia, the main indicators will be: difference in the prescription of 5 alpha-reductase inhibitors (finasteride and dutasteride, for which a reduction is expected); and difference in the ratio between the prescription of alpha blockers terazosin plus tamsulosin (already off patent drugs) versus other drugs of the same classes available in Italy (alfuzosin plus doxazosin – an increase of this ratio is expected). Secondary indicators will be: difference in the prescription of each of the alpha blockers listed above (a reduction is expected); difference of concomitant prescription of 5 alpha-reductase inhibitors and alpha blockers; and overall difference in expenditure for either 5 alpha-reductase inhibitors or alpha blockers (a reduction is expected for both of these indicators).

2. for the primary prevention of osteoporotic fractures, the main indicators will be: difference in the prescription of either alendronic acid or of sodium risedronate (a reduced increase is expected for both of these indicators, especially for the latter – for which the generic form is still unavailable). Secondary indicators will be: difference in the prescription of raloxifene and strontium ranelate (a reduction is expected for both of these indicators); and difference in the ratio between the prescription of alendronic acid (already off patent) versus the other two oral bisphosphonates available in Italy (sodium risedronate and ibandronic acid – an increase of this ratio is expected)

Physicians' expectations, perceived barriers and the added value about the proposed intervention will be eventually evaluated through focus groups with a sample of participating doctors for each region (at the end of the spring and the autumn rounds).

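### The Sardinia traditional-versus-enriched contrast compares two differently authored information packages, so a difference cannot be credited to format alone

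*Protocol article*

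**What the plan says.** All references are to the Protocol article.

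**The claim about format.** Under Objectives, the protocol asks "whether the format of information can affect the outcomes", with an enriched version set against a traditional one in Sardinia. Under Intervention/Exposure (Sardinia study) it states: "Both the effectiveness of the outreach visit and of the information format will be evaluated". The Background, the Figure 2 caption and the Discussion also speak of format. The Abstract is looser and describes the new format as "compared to information already available) on changing physicians' prescription of specific drugs".

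**The materials.** The enriched arm receives "the same kind of visit supported by an 'enriched' format (the type of bulletin used in the cluster study". In the cluster study, the pharmacist's role includes "discussing the contents of a bulletin specifically developed about the main studies/literature available on benefits and risks of drugs". For the traditional arm in round 1, "Two articles on that topic available in other drug bulletins have been eventually translated into Italian to be used for this scope"; this material "has been selected considering its availability and diffusion and its recognised dependability".

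**The outcome.** The traditional-versus-enriched comparison is listed among the secondary outcomes, for Sardinia only, in DDD per thousand inhabitants per day. The indicators for benign prostatic hyperplasia are set once for both studies. One of the two main indicators is a ratio whose numerator is "alpha blockers terazosin plus tamsulosin (already off patent drugs"), set against the other alpha blockers on the Italian market.

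**The concern.** A contrast shows the effect of format only if the same evidence and messages are presented in two ways. Here one arm is given a text written for the programme, and the other is given two texts written earlier, by other bodies, for other readers. Any of the following could produce a difference in prescribing: layout and clarity, the choice of studies, the strength and direction of the recommendations, or fit to Italian practice. Randomising GPs balances the physicians between arms, but it does not separate components bundled inside the intervention.

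What is at stake is the conclusion. A health authority that reads of an effect of format may decide to re-present existing material in the new style. If the effect came from content, that decision would rest on the wrong explanation. If there were no difference, it would be equally unclear whether format is unimportant or whether a content difference had masked it.

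**Working it through.** The article gives no figure for this point, so the check sets the relevant sections side by side.

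1. **What differs between the visited arms.** The enriched material was developed for the programme, and the traditional material consists of two existing articles from two other drug bulletins. The Economic analysis section confirms the separation: for Sardinia it counts the cost of developing the bulletin and, as a distinct item, the cost of translating the articles. Authorship therefore differs by design, and selection of evidence and messages may differ.

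2. **What is held constant.** The topic is the same, and the visit is described as being of the same kind. Pharmacist training is described once, with no distinction by arm.

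3. **What is not stated to be held constant.** The criteria given for the traditional material are that it "has been selected considering its availability and diffusion and its recognised dependability". Agreement with the bulletin on evidence or messages is not among them, and no other section states it.

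4. **What the three arms can identify.** Write N, T and E for the mean outcome with no visit, with a visit plus traditional material, and with a visit plus enriched material. Three means give two independent contrasts:
   - T − N = effect of a visit with the traditional package
   - E − T = F + C, where F is the part due to format and C the part due to content and authorship (taken as additive for simplicity)

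   The second line is one equation with two unknowns. The no-visit arm receives neither document, so it adds no information on F or C. F can be read from E − T only if C = 0, that is, if content was matched.

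5. **Visit versus no visit.** This contrast makes no claim about which feature of the material acts, so step 4 does not affect it.

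6. **The alpha-blocker ratio.** It depends on which drugs are off patent in Italy, which is country-specific, so it is reasonable to check whether both materials address it. The article does not describe the content of the two translated articles. It describes the bulletin type only as covering benefits and risks. It therefore does not show that either material carries the message or lacks it.

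7. **How many GPs the contrast involves.** About 900 GPs are expected and no allocation ratio is stated. Assuming equal arms, 900 / 3 = 300 per arm and 2 × 300 = 600 in the two visited arms. This is the number contributing to the contrast; it does not measure the bias.

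**The case against.** The strongest reply is that this is a pragmatic trial and that a new bulletin against existing, reputable articles is a legitimate comparison. The comparator and the way it was chosen are disclosed, the Abstract already sets the new format against information already available, and fit to the practice context can be seen as part of what enriched means. This stands as a defence of the comparison itself. It does not cover the wording elsewhere: Objectives, Intervention/Exposure and Discussion all attribute the contrast to format, and the Discussion explains the expected benefit by clear and appealing presentation.

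A second reply is that both arms get the same kind of visit, with no arm-specific training described, so a key message could reach GPs orally in either arm. That could shrink a content difference. It does not remove one, because the article does not say that the spoken messages were the same.

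A reader might go further and infer that the translated articles lack the off-patent message, that the bulletin was built to convey it, that the contrast is therefore biased towards the new bulletin, and that the ratio should be dropped from it. The article does not support these steps. Neither text is shown, the oral channel is open to both arms, and the format contrast is listed in DDD, without saying whether the ratio is also to be used for it.

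**Conclusion.** The point holds in a limited form. Format is confounded with content and authorship in the secondary traditional-versus-enriched contrast, which estimates the effect of a package. The conclusion rests on the different origin of the two materials and on the absence of any statement that their messages were matched. If the full protocol or the materials themselves show matched messages, the concern about content shrinks accordingly; different authorship would remain.

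No size can be put on C. It may be zero, account for the whole difference, or run against the format effect, and neither its presence nor its direction can be read from the article. The specific materials are known for round 1 only, since the second Sardinia topic is not given. Visit versus no visit stands as planned, so it would be wrong to infer that the Sardinia study as a whole is compromised. The issue deserves correction because the format question is a named objective and the reason for having two visited arms.

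**What to change.** 1. **Wording.** Restate the objective and the planned conclusion for this contrast as *new bulletin versus already available articles*, content and format together. This brings the other sections into line with the Abstract.

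2. **Round 1.** Before outcome data are seen, list the key messages of the bulletin and of the two translated articles. Interpret as format-related only those indicators whose message appears in both. The alpha-blocker off-patent ratio is one to check; whether it qualifies depends on what the materials turn out to say.

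3. **Round 2.** Since the Sardinia topic is still to be named, choose traditional material that carries the same key messages as the bulletin, and say so.

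The cost is a short message checklist, a few changes of wording, and some constraint on the choice of round 2 articles. No additional GPs or visits are needed. The downside is a narrower claim for the format comparison, possibly resting on fewer indicators.
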